### Sample size calculation

A RCT on the impact of e-mail promotion of self-help strategies for depression [15] showed that participants in the intervention group had modest but significant improvement in SSUS scores than those in the control group by a mean of 2.6 points, effect size d = 0.40. Assuming our study will achieve similar effect size, 258 participants (129 in each group) are needed to achieve the power of 0.80 at the α level of 0.05. The sample size calculation was done using STATA version 13. Assuming that the 12-month follow-up response rate is 75% with $20 incentive [10], we should recruit at least 344 participants (172 in each group) at baseline. Because the study will be carried out by sex separately, we proposed to recruit 350 men and 350 women who meet the inclusion criteria at baseline.

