## Methods/design

Given the background, the aim of the proposed randomized controlled trial is to answer the following research questions: (1) Does disclosure of personalized depression risk information promote high-risk individuals to take preventive actions? The effect of risk prediction may be maximized if these individuals actively engage in early prevention. (2) Will disclosure of personalized depression risk information negatively affect high-risk people’s mental health status? To safely implement the prediction algorithms, we need to ensure that the disclosure will not lead to increased psychological distress.

This study is a mixed-methods randomized controlled trial (RCT) with an embedded qualitative component. The RCT has one intervention arm (receiving personalized depression risk information) and one control arm (1:1). The target population are individuals in the community who are at high risk of major depression. The personalized depression risk is generated using the sex-specific MVRPs for MDE that we developed in Canadians aged 18+ years old [4]. Thus, the inclusion criteria are:
no MDE at baseline, or if had a MDE in the past 12 months, the individuals were in full remission for at least 2 months before the interview (see below the question),aged 18+ years,at high risk of MDE based on the algorithms (predicted risk of 6.5% + for men and of 11.2% + for women) [4],agreement to be contacted for follow-up assessments, andno language barriers to English or French.

The status of remission was assessed by the question: “In the past 2 months or longer, has your mood been much improved or back to normal AND you DIDN’T have the symptoms of.....?” This question was adopted from the US National Epidemiological Survey on Alcohol and Related Conditions [7]. Because the prediction algorithms are sex-specific, we are recruiting 350 men and 350 women at baseline. After baseline assessment for eligibility, participants are randomized into intervention and control groups, in men and women separately.

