### Intervention and control

For the participants in the intervention group, the personalized risk is disclosed and the interviewer informs the participants that they will be contacted again at 6 months and 12 months. The interest in receiving such personalized depression information has been confirmed by our recent pilot study using the same sampling method. Our pilot data (*n* = 200) showed that 100% of high-risk individuals were interested in knowing their risks. Participants in the intervention group are also informed that some may be contacted in 1 month for a 30-min qualitative interview. A package including the following materials is mailed to intervention participants: (1) thank-you letter, (2) general information about MDE, (3) self-help strategies [15] and a summary of research evidence supporting the effectiveness of self-help strategies, and (4) $20 incentive as appreciation of their participation. For participants in the control group, the interviewer informs them that they will be contacted again at 6 and 12 months. Their personal risks will be provided at the 12-month interview. They receive the same package as those in the intervention group.

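### The 129 per group does not follow from the stated inputs (d = 0.40 needs 99 to 100), and the 0.40 is not direct evidence for the effect of risk disclosure alone

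*Protocol article*

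**What the plan says.** The Sample size calculation section rests on the SSUS. Its effect size comes from "A RCT on the impact of e-mail promotion of self-help strategies for depression", in which the intervention group improved more than control "by a mean of 2.6 points, effect size d = 0.40". The section carries that value over and concludes: "Assuming our study will achieve similar effect size, 258 participants (129 in each group) are needed to achieve the power of 0.80", with alpha set at 0.05. It adds: "The sample size calculation was done using STATA version 13". It then allows for a 75% response at 12 months, which gives 344 (172 per group). Because men and women are studied separately, the target is set at 350 of each sex.

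Methods/design describes "one intervention arm (receiving personalized depression risk information) and one control arm (1:1"). Under Intervention and control, the mailed package contains self-help strategies and a summary of the evidence for them. Of the control participants it says: "They receive the same package as those in the intervention group". The Statistical analysis section analyses the sexes separately throughout.

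**The concern.** There are two separate problems.

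The first is arithmetic. The section gives an effect size, an alpha, a power and a resulting sample size, and the four do not agree. A reader cannot tell what effect the trial is powered for.

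The second is the relevance of the effect size. The 0.40 was seen when self-help strategies were promoted to one arm. In this trial self-help material goes to both arms, and the randomised difference is disclosure of the personal risk. The Background itself says that the literature on risk disclosure is absent in psychiatry and that it is unknown whether high-risk people will act on such information.

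The SSUS addresses the first research question and is the only outcome on which the trial is sized. A null SSUS result will be read against this power statement, so the statement should be numerically right and should not suggest more support for 0.40 than exists.

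**Working it through.** **Inputs.** d = 0.40, difference 2.6 points, alpha 0.05, power 0.80 and 75% response are from Sample size calculation; 1:1 allocation is from Methods/design. The sidedness of the test is not stated. Two-sided is assumed, and one-sided is also tried. The implied SD is 2.6/0.40 = 6.5 SSUS points.

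**Step 1: the plan's own figure.** For two independent means, n per group = 2 × (z₀.₉₇₅ + z₀.₈₀)² / d².

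- 2 × (1.960 + 0.8416)² = 15.70
- d = 0.40: 15.70 / 0.16 = 98.1, so 99 per group. The t-based figure is 99.08, so 100.
- Stated: 129 per group, about 30% more (129/99 = 1.30). It does not reproduce.

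**Step 2: power at 129 per group.** With d = 0.40, power is Φ(0.40 × √(129/2) − 1.960) = Φ(1.253) = 0.895. The t-based figure is 0.893. The stated power is 0.80.

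**Step 3: could another reading of the stated inputs give 129?**

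| Reading | n per group |
|---|---|
| d rounded, 0.395 to 0.405, 80% power | about 96 to 102 |
| One-sided alpha 0.05, d = 0.40, 80% power | 78 |
| 90% power, d = 0.40 (text says 0.80) | 132 (t-based 132.3) |
| d = 0.35, 80% power | 15.70/0.1225 = 128.1, so 129 (t-based 129.1) |
| Change-score variance, baseline correlation 0.345 (not stated) | 98.1 × 2 × (1 − 0.345) = 128.5, so 129 |

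Neither rounding nor sidedness explains the gap. The readings that come close all need an input that the section does not give.

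**Step 4: attrition.** 258/0.75 = 344 and 129/0.75 = 172. Both match the article, so the discrepancy lies in the first step only.

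**Step 5: what the enrolled sample can detect, per sex.** 350 × 0.75 / 2 = 131 per arm.

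- Smallest effect with 80% power: 0.350 SD at 129 per arm and 0.347 SD at 131. At SD 6.5 this is 0.35 × 6.5 = 2.3 SSUS points.
- Power with 131 per arm (t-based): about 90% at d = 0.40, 68% at d = 0.30 and 36% at d = 0.20. The last two effects are assumptions chosen to show a range; the article gives no estimate for disclosure.

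**Step 6: the contrast.**

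| | Tested arm | Control arm |
|---|---|---|
| Cited trial | E-mail promotion of self-help strategies | Not described in the article |
| This trial | Risk disclosure plus mailed self-help package | Same mailed package, risk disclosed at 12 months |

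The cited effect concerns promotion of self-help. The contrast randomised here is disclosure on top of self-help material that both arms receive.

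**The case against.** The strongest reply is that the error is harmless. At d = 0.40 the trial has more power than it claims, recruitment is complete, and the inflation for loss is right. That stands: a reader might infer from the mismatch that the trial is underpowered, and at its own effect size it is not. The arithmetic alone does not weaken a null result.

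A second reply is that the article condenses the calculation, and that a change-score variance or unrounded means and SDs could have been entered. This also stands in part. A reader might infer that the trial was really designed for d = 0.35, since that value returns 129 under the normal formula. The documents do not support this: 0.35 appears nowhere, the t-based need at 0.35 is 129.1, and an unstated correlation near 0.345 would give 129 as well. What survives is narrower: 129 does not follow from the inputs shown, and the text presents it as though it did.

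A third reply is that the article names its source openly and writes the effect as an assumption. That is fair. Nor may the mailed package be equated with the cited intervention: one is a single mailing, the other an e-mail promotion, and the cited trial's control condition is not described. The point is only that 0.40 is not direct evidence for disclosure alone.

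Finally, one could report detectable effects with men and women combined. The plan analyses the sexes separately, so the per-sex figures are the relevant ones.

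**Conclusion.** The concern holds in two limited parts.

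- **Sample size.** On the stated inputs, 99 to 100 per group are needed, not 129. With 129 per group, power is about 89% at d = 0.40, and 80% power is reached at about d = 0.35. This assumes a two-sided, 1:1 comparison of two means at alpha 0.05. The error is conservative at d = 0.40. Whether the effect size, the power or an unstated variance input accounts for it cannot be settled from the article.
- **Borrowed effect.** The 0.40 relates to promoting self-help strategies, and here both arms are mailed self-help material. It is not direct evidence for the randomised contrast. If disclosure has a smaller effect, power per sex falls to about 68% at d = 0.30 and 36% at d = 0.20 (assumed values, 131 per arm). The documents do not show that the effect is smaller, only that 0.40 has not been supported for it.

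The design is not invalidated. The power statement should be corrected before the SSUS result is interpreted against it.

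**What to change.** Change the text of Sample size calculation; enrolment, conduct and analysis stay as they are.

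1. Reconcile the inputs with the sample size. Either state that 129 per group gives about 89% power at d = 0.40 and that the smallest effect detectable with 80% power is about 0.35 SD per sex (about 2.3 SSUS points if the SD is 6.5), or state the further input, such as a change-score variance and its correlation, that yields 129. State that the test is two-sided if it is.
2. Replace the justification by a similar effect size with a caveat: the 0.40 comes from promoting self-help strategies and was not estimated for disclosure on top of a self-help package common to both arms.
3. Show per-sex power over a range of smaller effects, labelled as assumptions: with 131 per arm, about 68% at d = 0.30 and 36% at d = 0.20.

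The cost is a few sentences. The correction raises the stated power at d = 0.40, while the caveat makes the overall rationale more modest.

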## Discussion

### Current status

At the time of submission of this manuscript, we just completed baseline recruitment of 350 men and 350 women who meet the inclusion criteria. It is anticipated that the 6-month follow-up interviews will be completed by the end of September, 2019; 12-month follow-up interviews will be completed by the end of March, 2020.

### Potential risk and mitigation strategies

We acknowledge concerns about the changes in response rates in telephone surveys due to cell phone use and telemarketing. Including eligible participants across the country will enhance the generalizability of the study. Given the vast geographic area of Canada, RDD is the only feasible method. The goal of this study is to recruit participants for a RCT, rather than selecting a representative sample. In a RCT, selection bias is not a serious concern as long as the bias is the same across the intervention and control groups [24]. To mitigate the risk, the telephone survey firm will also access the validated cellphone database. However the use of cellphone numbers is associated with increased costs. Another potential risk of the proposed study is attrition which may incur selection bias. The population-based cohort studies on mental disorders in the workplace, conducted in our lab, showed that we could achieve 77% response rate at 1 year follow-up without any financial incentives [10]. Our strategies for reducing attrition will include appropriately designed introductory scripts, a minimum of nine call back attempts spaced over weekdays and times of day and provision of a $25 incentive for each completed interview.

Finally, those deemed low risk, who develops a MDE will be excluded from the RCT at the screening stage, which is a limitation. We have planned to provide the risk prediction algorithms so that they can monitor their risks in the future.

*Knowledge translation* will be in the form of peer-reviewed publications, conference presentations and research website dissemination. We will inform the stakeholders (decision makers and health professionals) who raised the pertinent questions in our previous KT activities, about the benefits of risk disclosure through the Canadian Depression Research Intervention Network and national professional organizations with which we are closely connected. The authorship of the publications generated from this trial will be determined according to the BMC Medical Research Methodology authorship guidelines. No scientific writers will be used.

A key step in early identification and prevention of MDE is the development and implementation of advanced tools for identifying individuals who are at high risk. Our team has developed the sex-specific MVRPs for MDE. The proposed trial will develop an evidence base for guiding the disclosure of personalized risk information and understanding the process of risk communication and consumer empowerment, contributing to the advancement of early prevention of MDE in Canada and beyond.

## Data Availability

Not applicable.

## Abbreviations

CIDI-SF: Composite International Diagnostic Interview – Short Form
DSM-IV: Diagnostic and Statistical Manual for Mental Disorders – 4th edition
ERB: Ethics review board
GAF: Global Assessment of Functioning
K10: Non-specific Psychological Distress Scale
MDD: Major depressive disorder
MDE: Major depressive episode
MVRP: Multivariable risk predictive algorithms
PI: Principal investigator
RC: Research coordinator
RCT: Randomized controlled trial
RDD: Random digit dialing
SSUS: Self-management strategy use scale
